## Abstract

**Background:**

People with schizophrenia are two to three times more likely to be overweight than the general population. The UK National Institute of Health and Care Excellence (NICE) recommends an annual physical health review with signposting to, or provision of, a lifestyle programme to address weight concerns and obesity. The purpose of this randomised controlled trial is to assess whether a group-based structured education programme can help people with schizophrenia to lose weight.

**Methods:**

Design: a randomised controlled trial of a group-based structured education programme.

Setting: 10 UK community mental health trusts.

Participants: 396 adults with schizophrenia, schizoaffective, or first-episode psychosis who are prescribed antipsychotic medication will be recruited. Participants will be overweight, obese or be concerned about their weight.

Intervention: participants will be randomised to either the intervention or treatment as usual (TAU). The intervention arm will receive TAU plus four 2.5-h weekly sessions of theory-based lifestyle structured group education, with maintenance contact every 2 weeks and ‘booster’ sessions every 3 months. All participants will receive standardised written information about healthy eating, physical activity, alcohol and smoking.

Outcomes: the primary outcome is weight (kg) change at 1 year post randomisation. Secondary outcomes, which will be assessed at 3 and 12 months, include: the proportion of participants who maintained or reduced their weight; waist circumference; body mass index; objectively measured physical activity (wrist accelerometer); self-reported diet; blood pressure; fasting plasma glucose, lipid profile and HbA_1c_ (baseline and 1 year only); health-related quality of life (EQ-5D-5L and RAND SF-36); (adapted) brief illness perception questionnaire; the Brief Psychiatric Rating Scale; the Client Service Receipt Inventory; medication use; smoking status; adverse events; depression symptoms (Patient Health Questionnaire-9); use of weight-loss programmes; and session feedback (intervention only). Outcome assessors will be blind to trial group allocation.

Qualitative interviews with a subsample of facilitators and invention-arm participants will provide data on intervention feasibility and acceptability. Assessment of intervention fidelity will also be performed.

**Discussion:**

The STEPWISE trial will provide evidence for the clinical and cost-effectiveness of a tailored intervention, which, if successful, could be implemented rapidly in the NHS.

**Trial registration:**

ISRCTN19447796, registered on 20 March 2014.

**Electronic supplementary material:**

The online version of this article (doi:10.1186/s13063-016-1572-1) contains supplementary material, which is available to authorized users.

## Background

Schizophrenia is a psychotic illness that affects approximately 1 % of the population. Mortality rates are increased two- to four-fold in people with schizophrenia and life expectancy is reduced by 10–20 years [1–3]. Approximately 75 % of all deaths in people with schizophrenia are caused by physical illness with cardiovascular disease being the commonest cause of death [1]. The prevalence of type 2 diabetes is increased two-fold in people with schizophrenia [4]. Overweight and obesity contribute to this excess morbidity and mortality. Recent studies indicate that obesity is two to three times more prevalent among people with schizophrenia than in the general population and this occurs early in its natural history [5].

The rates of overweight and obesity have increased substantially over the last three decades in people with schizophrenia and to a much greater extent than in the general population [6]. Reasons for this increase of obesity are complex and relate to environmental factors, such as poor diet and physical inactivity, as well as disease and treatment effects. Weight gain is a common adverse effect of antipsychotic medication, affecting between 15 and 72 % of patients [7]. Most weight gain occurs early in treatment with between 37 and 86 % of those experiencing a first episode of psychosis also experiencing more than 7 % weight gain in 12 months [8], often occurring within 12 weeks of treatment initiation [9]. Longer-term observational studies suggests that weight gain continues for at least 4 years albeit at a slower rate [10].

Individuals with schizophrenia are more likely to consume a diet that is rich in fat and refined carbohydrates while containing less fibre, fruit and vegetables than that of the general population [11–13]. Physical inactivity and the social and urban deprivation experienced by many people with schizophrenia may contribute further to their increased obesity rates [12–15]. These factors suggest that it may be possible to address the problem of obesity through appropriate lifestyle intervention.

A meta-analysis of nonpharmacological interventions in people with schizophrenia [16] has shown that these led to a mean reduction in weight of 3.12 kg over a period of 8–24 weeks. There were commensurate reductions in waist circumference and improvements in cardiovascular risk factors. The benefits of the programmes were seen irrespective of the duration of treatment, whether the intervention was delivered to an individual or in a group setting, whether the intervention was based on cognitive behavioural therapy or a nutritional intervention or whether it was designed to promote weight loss or prevent weight gain. There was overlap across intervention type, such that most cognitive behavioural therapy programmes also included a diet- or exercise-based intervention. Outpatient interventions appeared more effective than inpatient settings.

The meta-analysis, however, acknowledges a number of limitations of the trials, including small sample sizes and the lack of long-term follow-up. Most previous studies do not extend beyond 12 weeks and hence the impact of the interventions in the longer term remains unknown. The few studies reporting long-term effects suggest that these may persist after the end of the programme for up to 1 year but others suggest that long-term behaviour change is difficult to achieve [17]. The meta-analysis called for longer trials with larger numbers, with a focus on weight maintenance after the initial intervention.

The majority of evaluated weight-loss interventions, including diabetes prevention programmes, have utilised intensive one-to-one counselling strategies to promote behaviour change; however, these are challenging for direct implementation within current UK community care settings because of resource limitations [18]. Structured education is an alternative to one-to-one counselling and refers to group-based, patient-centred educational programmes that have a clear philosophy; have a written curriculum that is underpinned by appropriate learning and health behaviour theories; are evidence-based; and are delivered by trained, quality-assessed, educators [19]. Structured education has been widely advocated in England as a potentially cost-effective method of promoting self-management and behaviour change in individuals with chronic disease. Importantly, this approach has recently been adopted in the promotion of lifestyle change by the National Institute for Health and Care Excellence (NICE) diabetes prevention guidance [20].

The STEPWISE intervention is based on the diabetes prevention programme ‘Let’s Prevent Type 2 Diabetes’ [21] (often abbreviated to ‘Let’s Prevent’), which was developed by the Diabetes Education and Self-management for Ongoing and Newly Diagnosed (DESMOND) team.

DESMOND was the first nationally established, structured education programme and was originally designed for people with type 2 diabetes. The programme was effective at promoting lifestyle change, including weight loss, and reducing symptoms of depression in a multicentred randomised controlled trial (RCT) [22]. Let’s Prevent [23] is 6 h long and is designed to promote increased physical activity (specifically walking), a healthy diet through reduced fat and saturated fat intake and increased fibre, and weight loss by enabling participants to self-regulate their behaviour actively using self-monitoring (feedback), relapse prevention (identifying and addressing barriers to change) and goal-setting strategies. It also includes standardised educator/facilitator training and a quality assurance programme.

Given the rapid weight gain experienced by people with a first episode of psychosis [7], there is an urgent need to develop interventions that lead to long-term reductions in overweight and obesity. There is also a paucity of data in people with first-episode psychosis and so this group is included in the STEPWISE trial.

## Aims and objectives

The aim of the STEPWISE trial is to evaluate the extent to which a structured lifestyle education programme, when delivered to adults with schizophrenia, including those with schizoaffective disorder or first-episode psychosis, in a community mental health setting, can support weight loss at 1 year.

Having adapted the DESMOND ‘Lets Prevent’ intervention for people with schizophrenia, schizoaffective disorder or first-episode psychosis and their health care professionals [24], the specific objectives of the trial are:To undertake a multicentre RCT to test the hypothesis that a structured self-management lifestyle education programme can lead to a significant increase in physical activity and improved diet leading to clinically relevant weight loss after 1 yearTo ensure fidelity of the intervention when scaled up, through a robust assessment of its deliveryThrough qualitative research, to assess whether the intervention, when scaled up, is appropriate for and acceptable to mental health services and people with schizophrenia, schizoaffective disorder or first-episode psychosisTo undertake an economic evaluation of the interventionTo develop a quality assurance framework for facilitators delivering the intervention

## Methods

The trial is a multicentre, two-arm, parallel-group RCT of the STEPWISE structured lifestyle education programme. The trial design is summarised in Fig. 1. The study was planned and implemented in concordance with the Consolidated Standards of Reporting Trials (CONSORT) [25]. Public and Patient Involvement was actively sought in the development of the trial and will continue throughout the trial.

**Fig. 1 Fig1:**
[figure not shown]
Trial design

### Setting

The study will take place within community mental health teams (CMHTs), including early intervention services, in 10 mental health NHS trusts in the rural and urban locations of Sheffield, Bradford, Leeds and York, Greater Manchester, Somerset, Devon, Cornwall, Sussex, Hampshire and South London.

### Participants

Adults are eligible for inclusion in the study if they:Are aged 18 years or olderHave a diagnosis of schizophrenia or schizoaffective disorder (defined *by International Classification of Diseases, version 10* (ICD-10) codes F20, F25) or first-episode psychosis (defined as less than 3 years since presentation to the mental health team) using case note reviewAre being treated with antipsychotic medication; for those with schizophrenia or schizoaffective disorder, the treatment duration should be at least 1 month prior to entry into the trialAre able to give written informed consentAre able and willing to attend and participate in a group education programmeAre able to speak and read EnglishHave a Body Mass Index (BMI) ≥25 kg/m^2^ or are concerned about their weight. For participants from South Asian and Chinese backgrounds, the BMI threshold is reduced to ≥23 kg/m^2^

People are excluded from the study if they have a:Physical illness that could seriously reduce their life expectancy or ability to participate in the trialA coexisting physical health problem that would, in the opinion of the principal investigator, independently impact on metabolic measuresMental illness that could seriously reduce their ability to participate in the trialCurrent pregnancy or are less than 6 months postpartumA condition associated with significant weight gain, e.g. Cushing’s syndromeSignificant alcohol or substance misuse, which, in the opinion of the principal investigator, would limit the patient’s ability to participate in the trialA diagnosis or tentative diagnosis of psychotic depression or maniaA primary diagnosis of learning disability

People will also be excluded if they are currently (or within the past 3 months) engaged in a systematic weight management programme.

### Selection and randomisation

The trial will be promoted within clinical teams and in areas where community mental health services are delivered. Members of the research team will work with clinical teams within the mental health trust to identify potentially eligible patients from their caseload. Patients can also self-refer, using information displayed on posters or leaflets, if they are interested in taking part.

After baseline assessments, participants will be randomised using the Sheffield Clinical Trials Research Unit’s (CTRU) remote randomisation system. A randomisation list generated using permuted blocks of random sizes will be used to allocate the participants to either treatment as usual (TAU) plus the STEPWISE lifestyle education programme or TAU alone in a 1:1 ratio, stratified by site and time since the start of antipsychotic medication (up to 3 months or longer than 3 months). Where the exact time is unknown, an approximate duration will be acceptable for the purposes of randomisation.

A member of the site team will inform the participants of their allocation. Outcome assessors will be blind to treatment allocation. Blind (or suspected) breaks will be recorded on the Case Report Form and reported periodically to the trial oversight committees. Due to the nature of the intervention participants cannot be blinded.

### Research intervention

#### Precourse information

Participants allocated to the research intervention will be contacted by the session coordinator (administrator) and provided with precourse information (e.g. an introductory letter and leaflet), which will confirm when the sessions will take place and what to expect.

#### STEPWISE education programme

The intervention lasts for approximately 12 months. Participants allocated to the intervention will receive a foundation course of four weekly 2.5-h (including breaks) group sessions delivered by two trained facilitators. The group sessions will involve approximately six to eight participants, although this may vary due to recruitment and attrition. The foundation course will be followed by 1:1 support contact lasting about 10 min, approximately every 2 weeks for the remainder of the intervention period, from a facilitator in order to support behaviour change. Ideally, support contact will be personalised and carried out face-to-face or by telephone. Participants will be invited to attend group-based booster education sessions at 4, 7 and 10 months post randomisation. Group attendance and receipt of support contact will be recorded.

Intervention sessions include: individual personal stories; taking control of weight; healthier food and drink choices; the relationship between weight and medication; and the relationship between calories and portions and physical activity (see Additional file 1). The intervention has a written curriculum to ensure consistency and resources that are in line with meeting its person-centred philosophy. Participants will not be ‘taught’ in a formal way, but rather supported to discover and work out knowledge for themselves, and to allow this to inform their goals and plans.

Participants attending education sessions will be invited by facilitators to complete a ‘Session Feedback’ form at the end of each session. The aim is to capture a self-report of empowerment and health belief during the course; the facilitators will not read the forms. Participants are not encouraged to bring someone with them to the intervention sessions; however, if they do, this will be documented.

#### Facilitator training

At least four health care professionals or associated staff at each location will receive facilitator training to deliver the STEPWISE education programme. Training comprises: the core DESMOND philosophy (1 day); and, specific content and delivery of the STEPWISE programme including content and delivery of booster sessions and support contact (3 days). Training will be preceded by a set of preparation exercises. Training will follow the philosophy and psychological principles that underpin patient education initiatives.

### Control arm

Participants in the control arm will receive TAU. There is significant variability in the provision of physical health care, despite the NICE guidelines on treatment and management of schizophrenia regarding healthy eating and physical health [26].

In order to standardise usual care in both groups, as far as possible, centres will provide printed advice to all participants at baseline (prior to randomisation) on the risk of weight gain and lifestyle advice, including information about diet and physical activity, and smoking and alcohol use (as appropriate). We will record any uptake of weight management and/or physical activity programmes by all participants during the study, and collate information from centres about uptake of NICE recommendations more widely.

### Outcome measures

Consistent with the primary objective of this trial, the primary endpoint is change in weight (kg) at 12 months after randomisation.

Secondary outcomes include: proportion of participants who maintained or reduced their weight, waist circumference, body mass index, physical activity captured via wrist accelerometer, blood pressure, fasting plasma glucose, lipid profile and HbA_1c_; behaviour change (self-reported diet; smoking status) and psychosocial factors including quality of life (RAND SF-36 [27]and EQ-5D-5L [28]); health beliefs (adapted Brief Illness Perception Questionnaire [29]; Brief Psychiatric Rating Scale [30]) and cost-effectiveness (Client Service Receipt Inventory [31]). Secondary outcomes also include: medication use; adverse events; depression symptoms (Patient Health Questionnaire-9 [32]); use of weight-loss programmes; and session feedback (intervention participants only). All outcome measures will be assessed at baseline and after 3 and 12 months (except where stated) to measure if there is an effect and, if so, whether this is sustained in the longer term. Follow-up windows for 3- and 12-month follow-ups will be defined as minus 2 weeks and plus 4 weeks to allow time for missed appointments. A schedule of enrolment, interventions, and assessments based on the SPIRIT 2013 Figure [33] is shown in Fig. 2.

**Fig. 2 Fig2:**
[figure not shown]
SPIRIT Figure – Schedule of enrolment, interventions, and assessments, based on recommendations for Interventional Trials (SPIRIT) figure, for the STEPWISE trial. Following enrolment, all participants receive written lifestyle information; and, before collection of 0 month assessments. Participants are then randomised to either usual care with structured education or usual care. Participants allocated to structured education are invited to: a) 4 weekly 2.5 hour group sessions (delivered by trained facilitators); group booster sessions at 4, 7 and 10 months post-randomisation; and, 1:1 support contact between month 2 and month 12. Research assessments are completed with all participants at 0, 3 and 12 months (as indicated)

The research nurse or clinical studies officer will administer all questionnaires and other assessments either at the participant’s home or in the NHS trust. Additional information (e.g. medication) may be obtained from the patient’s notes. All participants will receive a £20 voucher at the 12-month assessment.

The operational criteria OPCRIT Checklist for psychotic and affective illness will be completed from case note review within 10 weeks post baseline visit to provide baseline characteristics. Collection of fasting blood sample and accelerometer data will be permitted after randomisation where recruitment is close to the scheduled education course.

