### Data analysis

Data will be analysed and reported according to the guidelines of the revised CONSORT statement for randomised controlled trials [25].

The analysis will be performed on an intention-to-treat basis and all statistical tests will be two-tailed at 5 % significance level. Demographics and baseline characteristics will be summarised and assessed for comparability between the intervention and control arms [38, 39].

The primary outcome will be assessed by fitting a marginal generalised estimating equation model (GEE) adjusted for baseline weight, using robust standard errors and an exchangeable correlation structure. This model incorporates an adjustment for potential clustering or correlation among the outcomes of participants treated in the same group. A 95 % confidence interval for the difference in weight between the lifestyle intervention and control arms will be reported with its associated *P* value. A sensitivity analysis will be performed in the same manner, which will include baseline covariates and any observed imbalances. In case of missing data, the missing data mechanism will be explored and multiple imputation approach applied to assess the robustness of the findings.

Of key interest is whether the intervention conveys the same effect among recently diagnosed patients (i.e. patients experiencing first-episode psychosis) as it does among those established on antipsychotic medication for a greater period of time. We will investigate this in the analysis by fitting an interaction term between treatment group and the time since starting antipsychotic medicine (including a nonlinear term if appropriate). The treatment effect will be presented graphically for different subgroups of the time elapsed since commencing medication.

Other continuous outcomes will be analysed and reported in the same manner as the primary outcome. Analysis of binary outcomes will be undertaken using a marginal generalised logistic linear regression model within the GEE framework and difference between treatment groups will be reported as odds ratios with associated 95 % confidence intervals and *P* values.

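### Baseline accelerometer and fasting blood data may be collected after allocation is known, and may then bias baseline-adjusted secondary comparisons, chiefly physical activity

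*Protocol article*

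**What the plan says.** Under Selection and randomisation, the protocol article gives the usual order: "After baseline assessments, participants will be randomised". The Fig. 2 legend agrees; it places the 0-month assessments first and continues "Participants are then randomised to either usual care with structured education or usual care".

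The text after that legend makes an exception for two items: "Collection of fasting blood sample and accelerometer data will be permitted after randomisation where recruitment is close to the scheduled education course". No such exception is made for weight.

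On blinding, Selection and randomisation says "A member of the site team will inform the participants of their allocation" and "Due to the nature of the intervention participants cannot be blinded". It also says "Outcome assessors will be blind to treatment allocation".

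The measurements concerned are secondary outcomes, listed under Outcome measures as part of "physical activity captured via wrist accelerometer, blood pressure, fasting plasma glucose, lipid profile and HbA_1c". Blood pressure is in that list but is not covered by the exception.

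Data analysis adjusts the primary model (a GEE) for baseline weight and then says "Other continuous outcomes will be analysed and reported in the same manner as the primary outcome".

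Protocol changes adds that sites were encouraged to recruit shortly before each course, which is the situation in which the exception applies.

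**The concern.** A baseline covariate is safe to adjust for because it is fixed before anyone knows the allocation. A value taken afterwards does not have that protection. An intervention participant who expects the course, or has begun it, may already be more active or eating differently. A control participant may react to being allocated usual care. If the late values differ by arm for such reasons, adjusting for them changes the estimated treatment effect.

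Accelerometer activity is the most exposed because it can change within days, and the first objective names increased physical activity as part of the route to weight loss. Glucose and lipids are less exposed. HbA1c moves slowly and is least exposed. Knowing the allocation could also make completion of the late measurements differ between arms.

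**Working it through.** The plan gives no figure to reproduce here, so the check has two parts.

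**1. What the text fixes**

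- Every 3- and 12-month measurement is post-randomisation in any case. A permission to collect after randomisation therefore has meaning only for the baseline measurement, and it contradicts the order stated in Selection and randomisation and in the Fig. 2 legend.
- The article states no time limit on late collection and no requirement to finish before the first session.
- Adjustment of each continuous outcome for its own baseline is inferred from the same-manner sentence. It is the natural reading, although only weight is named.

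**2. Size of the possible bias**

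The document gives none of these inputs, so all are assumptions:

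- b: slope of follow-up on baseline
- f: share of baselines collected late, taken as equal in both arms
- d: mean shift in the late values, intervention minus control, caused by knowing the allocation or by early sessions
- τ: true effect at follow-up

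In a linear baseline-adjusted model, the late values move the arm difference at baseline by f × d, so

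estimate ≈ τ − b × f × d.

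Writing d = s × τ, where s is the fraction of the final effect already present in the late value,

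estimate ≈ τ × (1 − b × f × s), a proportional loss of b × f × s.

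| b | f | s | Loss, b × f × s |
|---|---|---|---|
| 0.3 | 0.1 | 0.1 | 0.003 = 0.3% |
| 0.5 | 0.25 | 0.5 | 0.0625 ≈ 6% |
| 0.7 | 0.5 | 0.5 | 0.175 = 17.5% |

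Simulation with 400,000 participants per scenario and τ = 0.300 gave 0.281 for the second row (formula: 0.300 × 0.9375 = 0.281) and 0.247 for the third (formula: 0.300 × 0.825 = 0.2475).

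If the same manner instead meant an unadjusted change from baseline, the loss would be f × s: 0.25 × 0.5 = 12.5% and 0.5 × 0.5 = 25% in those two rows.

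The sign depends on d. If the late intervention values have moved in the direction of benefit, d has the sign of τ and the estimate is attenuated. If controls move further in that direction than intervention participants, d has the opposite sign and the effect is exaggerated. If no late value depends on arm, d = 0 and there is no bias.

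**The case against.** The strongest reply is that this is a disclosed, practical exception whose effect may be trivial. The intervention lasts about 12 months, with a four-week foundation course, fortnightly support and boosters at 4, 7 and 10 months. A measurement made around the start of the course should contain little of the eventual effect. That stands, and it is why s belongs in the calculation.

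A reader might infer a loss of 5% to 35% by multiplying an assumed late share of 10% to 50% by a slope of 0.5 to 0.7 (0.1 × 0.5 = 5%; 0.5 × 0.7 = 35%). That sets s = 1, so the late value would already hold the whole follow-up effect. The document does not support this, and it gives no late share either.

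A second reply is that a full protocol may limit late collection, and an analysis plan may say how late baselines are handled. Neither is shown, so the absence of such detail is not the point. The point is the stated permission: followed together with the stated analysis, it makes a post-randomisation value a baseline covariate.

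A third reply is that outcome assessors are blind. That protects the measurement, but not the behaviour of participants who know their arm.

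Finally, discarding every late value loses some that are probably close to true baselines. That is fair, and it is a reason to keep the analysis using them as a sensitivity analysis.

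**Conclusion.** The contradiction over timing is plain in the text. The bias is possible, not established. It needs late values that differ by arm because of known allocation or early sessions, and it rests on reading the same-manner sentence as adjustment for each outcome's own baseline. Its size cannot be derived from the document: the partial-effect examples run from 0.3% to 17.5% of the true effect, all on assumed inputs, and its direction is not certain.

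A reader might go further and conclude that the trial's main result, or all the metabolic results equally, are compromised. The document does not support that. Weight is outside the permission, no mediation analysis of the weight result is described, and the exposure falls mainly on accelerometer activity.

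This is worth correcting before unblinded analysis, but because only secondary outcomes are at risk it is not a condition for the trial's validity.

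**What to change.** Reconcile Selection and randomisation and the Fig. 2 legend with the text that follows the legend, so that the timing of these two baseline items is stated once. Trial status reports that recruitment closed on 31 March 2016, so withholding the allocation until the items are collected is no longer possible and the remedy lies in the analysis.

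Before unblinded analysis, specify the following:

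- Compare each collection date with the date allocation was disclosed, or with the randomisation date if disclosure was not recorded.
- Treat accelerometer and blood values collected after that date as missing baseline. Handle them in the same way as baselines never collected, so that completion of late measurements that differs by arm cannot matter.
- Impute these baselines without using arm, for example with the mean of the valid baselines pooled over arms, and keep every participant in the analysis.
- Report the number of late collections by arm.
- Give the analysis that uses the late values as a sensitivity analysis.

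With late values removed from the covariate, d = 0 and the bias term is zero. The cost is a date comparison, a few lines of analysis text and slightly lower precision for these secondary outcomes. The rule must be set before unblinding, because choosing afterwards which baselines count would be data-driven.
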